### Outcome measures

Outcome data will be collected at baseline (prior to randomisation), and then 10 weeks (±2 weeks) and 6 months (±4 weeks) after randomisation by independent blinded assessors. The baseline and 10-week assessments will be conducted face-to-face and the 6-month assessments will be conducted by telephone. For this reason, motor and sensory scores and AIS grades will not be collected at 6 months. The success of assessor blinding will be monitored and reported.

#### Primary outcome measure

The primary outcome is Total Motor Score (/100 points) 10 weeks after randomisation according to the International Standards for the Neurological Classification of SCI [2, 35].

#### Secondary outcome measures

The following 11 secondary outcomes will be collected (see Table 2 for the timing of each):American Spinal Injuries Association Impairment Scale [2, 35].Upper Extremity Motor Score [2, 35].Lower Extremity Motor Score [2, 35].Total Sensory Score [2, 35].Spinal Cord Independence Measure Version III—Self Report [36].Walking Index for Spinal Cord Injuries Version II [37].The World Health Organization Quality of Life—BREF [38] (the 4 domains will be analysed separately).EUROQOL—5D Health Questionnaire [39].Participants’ perceptions about ability to perform self-selected goals (based on the Goal Attainment Scale [40, 41] and the Canadian Occupational Performance Measure [42]).Participants’ impressions of therapeutic benefit [43].Time to discharge.

**Table 2 Tab2:** The assessment schedule.

	Enrolment	Baseline	0–10 weeks	10 weeks	6 months
Preliminary data/processes					
Inclusion/exclusion criteria	✓		Intervention period		
Demographic details		✓			
Date of injury		✓			
Outcomes					
Total motor score		✓		✓	
AIS grade		✓		✓	
The Upper Extremity Motor Score		✓		✓	
The Lower Extremity Motor Score		✓		✓	
Total sensory scores		✓		✓	
SCIM-III		✓		✓	✓
WISCI-II		✓		✓	✓
WHOQOL-BREF (4 domains)		✓		✓	✓
The EQ-5D-5L		✓		✓	✓
Participants’ perceptions about ability to perform self-selected goals		✓		✓	✓
Participants’ impressions of therapeutic benefit				✓	✓
Time to discharge					✓

In addition, participants in the Motor Training Group will be asked to rate their perceptions of the benefits and harm from the intensive motor training. A second question will be asked about the burden of the intensive motor training using a similar format. Participants will be invited to provide any comments to help better understand their perceptions.

### Sample size

A sample size of 220 is needed to provide a 90% probability of detecting a significant between-group difference of 6/100 points on the Total Motor Score (/100 points) 10 weeks after randomisation. The decision to use 6/100 points is based on the recommendations of the Committee representing The International Campaign for Cures of Spinal Cord Injury Paralysis (ICCP) [44]. The committee states that 5 to 10 points reflects a “relatively modest treatment effect”. These calculations assume a SD of the change in Total Motor Scores of 13.3 points, a worst-case loss to follow-up in both groups of 10%, and an alpha value of 0.05. The estimated SD is based on comprehensive data from a large trial provided by the ICCP, and takes into account the exclusion of people with complete injuries and no zones of partial preservation, and the delayed recruitment for up to 10 weeks after injury (see Supplementary Fig. 2, pg 2, 2nd column, 3rd row in reference [44]). Allowance has been made for one interim analysis using the O'Brien-Fleming stopping rule.

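### The inputs listed for the sample size lead to about 231 to 232 participants, not 220; the gap is small, and the planned baseline adjustment may close it

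*Protocol article*

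**What the plan says.** The Sample size section of the protocol article gives a result and the inputs behind it.

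- Result: "A sample size of 220 is needed to provide a 90% probability of detecting a significant between-group difference of 6/100 points". The endpoint is the 10-week Total Motor Score.
- Variability: "These calculations assume a SD of the change in Total Motor Scores of 13.3 points".
- Attrition and significance level: "a worst-case loss to follow-up in both groups of 10%, and an alpha value of 0.05".
- Interim look: "Allowance has been made for one interim analysis using the O'Brien-Fleming stopping rule".

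Three other sections bear on the check. Assignment of intervention describes two groups and gives no allocation ratio. Data monitoring places the interim analysis at 110 participants who have completed the trial. Data analysis, Primary outcome, specifies a mixed linear model for the 10-week score, with group, injury severity and baseline motor score as covariates and site as a random effect. It says that baseline is included for precision.

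**The concern.** The paragraph lists difference, SD, loss, alpha, power and interim rule next to the sample size, so the calculation can be repeated. When it is, 220 does not come out. The figure is too low for a design that is meant to hold 90% power after 10% loss, and it is close to what a 5% loss would require.

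Power and the loss allowance are the figures against which a null result and the actual attrition will be judged. The paragraph presents 10% as a worst case, which tells the reader that 90% power survives a loss of that size. On the listed inputs it does not quite do so.

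**Working it through.** **Inputs.** Difference 6, SD of change 13.3, alpha 0.05, power 90%, loss 10%, one O'Brien-Fleming interim (all from Sample size); interim at 110 completers (Data monitoring). Two-sided alpha and 1:1 allocation are assumptions.

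**1. What reproduces 220.** A fixed design needs, per arm,

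n = 2 × (1.960 + 1.282)² × 13.3² / 6² = 103.26, rounded up to 104.

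With 5% loss, 104 / 0.95 = 109.5, so 110 per arm and 220 in total. The stated loss is 10%.

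**2. The stated 10% loss, no interim.** 2 × 103.26 = 206.5 evaluable, and 206.5 / 0.90 = 229.5 randomised. From 104 per arm, 208 / 0.90 gives 232 after rounding. So 220 is already too few before the interim is considered.

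**3. Adding the interim.** The bounds come from the bivariate normal distribution of the two test statistics.

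| Look at | Bounds | Inflation | Evaluable | Randomised (÷ 0.90) |
|---|---|---|---|---|
| 0.50 of information | 2.797 / 1.977 | 1.0071 | 207.99 | 231.1 |
| 110/198 = 0.556 | 2.664 / 1.985 | 1.0100 | 208.58 | 231.8 |

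Equal arms make this 232. The interim costs little; nearly all of the gap comes from the loss allowance.

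**4. Other conventions.**

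- Lan-DeMets O'Brien-Fleming-type spending: 230.2 to 230.8 randomised.
- t-test in place of the normal approximation, with the interim: 232.4 to 233.9.
- Multiplying by 1.10 instead of dividing by 0.90, normal approximation: 227.2 without the interim, 227.9 to 229.4 with it.
- One-sided alpha 0.05: about 189.

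None of these gives 220.

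**5. Power at 220 randomised.** 220 × 0.90 = 198 evaluable, 99 per arm.

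- No interim, normal: 6 / (13.3 × √(2/99)) = 3.174; 3.174 − 1.960 = 1.214; power 88.8%.
- No interim, t-test: 88.5%.
- Classical O'Brien-Fleming interim, normal: 88.5% (look at 0.50) or 88.45% (look at 0.556).
- With no loss at all (220 evaluable) and the interim: about 91.5%.

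**6. Loss at which 220 still gives 90%.** 1 − 207.99/220 = 5.5%, or 1 − 208.58/220 = 5.2% with the look at 110 of 198.

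**7. Detectable difference at 90% power, 198 evaluable.** 6 × √(207.99/198) = 6.15 points.

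**8. What baseline adjustment would have to deliver.** The residual SD that restores 90% with 198 evaluable is 13.3 × √(198/207.99) = 12.98, or 13.3 × √(198/208.58) = 12.96. That is a variance reduction of about 5%. Since √0.05 ≈ 0.22, it corresponds to a correlation of about 0.22 in size between baseline score and change.

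If the baseline and 10-week variances are equal, the ratio of adjusted to change-score variance is (1 + ρ)/2, where ρ is the correlation between the two scores. Setting (1 + ρ)/2 = 0.95 gives ρ of about 0.90 or lower. The article gives no ρ, so the following is a range over assumed values (198 evaluable, normal approximation, before the interim):

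| Assumed ρ | Residual SD | Power |
|---|---|---|
| 0.70 | 12.26 | 93.1% |
| 0.80 | 12.62 | 91.7% |
| 0.90 | 12.96 | 90.3% |
| 0.95 | 13.13 | 89.5% |

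**The case against.** The strongest reply is that 88.5% belongs to an analysis the trial will not run. The SD of 13.3 is for change scores, whereas the primary model adjusts for baseline score and injury severity. In large samples the baseline-adjusted residual SD cannot exceed the change-score SD, so 88.5% is close to a floor for the planned analysis, and a variance reduction of about 5% restores 90%. This stands. A reader might infer that the trial itself has only 88.5% power. The article does not support that: it gives no correlation, and over much of the range shown the adjusted analysis is at or above 90%. Equally, it does not show that the credit was taken. The paragraph names the change-score SD and mentions no adjustment, so a reader cannot assume an unstated credit that happens to offset the gap.

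Secondly, the gap is small: 1.5 points of power, or 6.15 points instead of 6, at a loss described as the worst case. The SD is itself an estimate adapted from another trial's data. This also stands, and it bears on severity. It does not make the listed figures agree.

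Thirdly, an article condenses a full protocol that is not shown and that may contain the formula. That would excuse a missing detail, but here the inputs and the result are both printed and do not match. It does limit what can be said about the cause. A reader might conclude that 5% was used by mistake for 10%, or that the allowance was left out. The 5% figure fits, but the article does not establish how 220 was reached.

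**Conclusion.** The point holds as an inconsistency within the Sample size section. On its listed inputs, with two-sided alpha 0.05 and 1:1 allocation assumed, 90% power needs about 231 to 232 randomised, so 220 is about 5% short (12 / 232 = 5.2%). At 220 with the stated 10% loss, an unadjusted change-score comparison has about 88.5% power, a type II error of 11.5% instead of 10%. It keeps 90% only up to a loss of about 5%.

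Severity is minor. A reader might take this as evidence of an underpowered trial, and it is not. The figure applies to an unadjusted analysis at worst-case loss, and the planned baseline-adjusted model may reach 90% or more. Whether it does depends on a correlation that the article does not report.

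**What to change.** Keep 220 and make the paragraph agree with its inputs, for example:

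> With 220 randomised and a worst-case 10% loss (198 evaluable), SD of change 13.3, two-sided alpha 0.05, 1:1 allocation and one O'Brien-Fleming interim, power to detect 6 points is about 88.5% before any credit for baseline adjustment. Power of 90% is reached if loss is no more than about 5%, or if the residual SD after adjustment is no more than about 12.97.

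If the calculation actually used a 5% loss, or a residual SD after adjustment, state that figure and its basis instead. Two-sidedness and the allocation ratio should be confirmed in either case.

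The cost is a change of wording, with a slightly less favourable power statement if the first option applies. No participants, analyses or decision rules change.

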### Data analysis

#### Primary outcome

The mean between-group difference in Total Motor Scores at 10 weeks will be estimated with a mixed linear regression model in which Total Motor Score at 10 weeks will be regressed on randomised group, baseline severity of injury (a stratification variable), and baseline motor score. Site (a second stratification variable) will be included as a random effect. Baseline scores will be included in the model to increase precision [45]. Severity of injury and study site will be included in the model to prevent the anti-conservative bias in standard errors that would otherwise be produced by stratification on these variables [46]. The effect of the intervention will be estimated as the adjusted mean between-group difference and confidence interval.

The primary analysis will be performed without replacing missing data. It will be expected to provide unbiased estimates of the intervention effect if data are missing at random conditional on non-missing data [47]. In case of non-negligible amounts of missing primary outcome data at 10 weeks (>5%), we will use controlled multiple imputations to assess under what conditions the results change, and how plausible these conditions are, using the approach described by Cro et al. [48].

A subgroup analysis will examine whether the effect of the intervention is moderated by the type of SCI at baseline (AIS A or AIS C/D), and severity of injury (paraplegia or tetraplegia). The subgroup analysis will be conducted on the primary outcome using a model that is the same as the linear regression model used in the primary analysis except that it contains, in addition, a term for the interaction between group and type of SCI.

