### Assignment of intervention

A blocked randomisation schedule stratified by site and severity of injury (paraplegia or tetraplegia) that incorporates random permuted blocks has been computer-generated by an investigator who is not involved in the day-to-day running of the trial. The schedule was uploaded onto REDCap with strict control of user rights to ensure concealment from potential participants, trial staff and investigators.

Randomisation will occur after consent has been given and the baseline assessment has been completed. The assessor will send an email request for allocation, whereupon a researcher who is otherwise not involved in the trial will log into the REDCap database, triggering the randomisation and sending of an automated email notification to the participant’s site. Allocation will be to one of two groups: a Motor Training Group or a Usual Care Group. Both groups will continue to receive usual physiotherapy and rehabilitation.

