#### Secondary outcomes

The effect of the intervention on upper and lower limb strength, sensation, independence, ability to walk, quality of life, perceptions of the ability to perform self-selected goals, and impressions of therapeutic benefit will be estimated using the same statistical model used in the primary analysis. For outcomes measured at both 10 weeks and 6 months, both visits will be included in the model and correlations between repeated measures will be modelled by including a random patient intercept and the effect of the intervention will be estimated at each visit by a fixed term for visit together with its interaction with the intervention.

Similar models will be used to estimate the effect of the intervention on participants’ impressions of therapeutic benefit. However, as baseline values are not collected for this outcome variable, baseline Total Motor Score will be used in the model as a pre-randomisation covariate.

The effect of the intervention on time to discharge will be estimated from a Cox model that includes baseline Total Motor Score and the stratification variables (severity as a fixed effect and site as a random effect). Patients will be censored at 6 months or when they were last known to be in hospital, whichever occurs earlier.

The effect of the intervention on type of SCI (AIS grade—5 levels) will be estimated using an ordinal logistic regression model that includes baseline AIS grade and the stratification variables. The effect of the the intervention will be estimated as the odds ratio corresponding to the odds of shifting to a worse grade category.

No subgroup, adjusted or imputed analyses are planned for any of the secondary outcomes.

If there is more than 20% non-adherence (defined as less than 80 h of additional motor training), methods of causal inference will be used to estimate the effects of intervention in the principal stratum of people who would comply with both assigned and (counterfactual) unassigned interventions [49]. Modern methods of causal mediation analysis will also be used to determine the extent to which the effects of the intervention are mediated by time spent in training [50, 51].

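### The primary model is valid but omits baseline AIS grade and time since injury, two already-recorded covariates that could add precision at little cost

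*Protocol article*

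**What the plan says.** Under Data analysis, Primary outcome, "Total Motor Score at 10 weeks will be regressed on randomised group, baseline severity of injury (a stratification variable), and baseline motor score". The next sentence adds that "Site (a second stratification variable) will be included as a random effect". Each term has a stated reason: the stratification variables protect the standard errors, and "Baseline scores will be included in the model to increase precision".

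Under Assignment of intervention, the schedule is "stratified by site and severity of injury (paraplegia or tetraplegia"). The severity term is therefore neurological level in two categories. It is not AIS grade.

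Table 2 ticks AIS grade and "Date of injury" in the baseline column. Under Outcome measures, "Outcome data will be collected at baseline (prior to randomisation"), so both are pre-randomisation variables. Table 1 admits AIS A with some preserved motor function, AIS C and AIS D, injured at any time in the previous 10 weeks. Both variables can therefore differ between enrolled participants.

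AIS type appears twice more in the analysis plan. AIS A versus C/D is a subgroup factor for the primary outcome, and the AIS outcome is analysed with an "ordinal logistic regression model that includes baseline AIS grade and the stratification variables".

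**The concern.** The plan adjusts for baseline motor score to gain precision. The same reason extends to any other variable that is fixed before randomisation and predicts the 10-week score. AIS grade and time since injury are plausible candidates. They are on file for participants because eligibility depends on them, and they are not balanced by design. Baseline motor score does not carry days since injury, and the same total can arise with different levels and completeness of injury.

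If the two variables predict outcome beyond the planned covariates, leaving them out puts avoidable variance into the residual and widens the confidence interval for the treatment effect.

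There is also a structural point. The subgroup model is described as the primary model with one further term, the interaction of group with type of SCI. Type of SCI (AIS A or C/D) is not in the primary model. Read literally, the subgroup model has an interaction without its main effect.

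**Working it through.** **Inputs.** From Sample size: difference 6 points, SD of change 13.3, alpha 0.05, power 90%, 220 randomised, 10% loss. Assumed because not stated: two-sided test and 1:1 allocation. Evaluable: 220 × 0.9 = 198, or 99 per arm.

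**The plan's own figure.** SE = 13.3 × √(2/99) = 1.890. Power = Φ(6/1.890 − 1.960) = 88.8% (88.5% from the t distribution). This is close to the stated 90%. In the other direction, n per arm = 2 × (13.3 × (1.960 + 1.282)/6)² = 103.3, rounded up to 104. That is 208 evaluable and 208/0.9, or 232, randomised, against the planned 220.

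**Effect of adding the two covariates.** Let R² be the share of residual variance that AIS grade and time since injury explain once group, paraplegia/tetraplegia, baseline motor score and site are in the model. The article gives no value, so a range is assumed. Residual SD = 13.3 × √(1 − R²), with the same power formula.

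| Assumed partial R² | Residual SD | SE | Reduction in SE | Power, 99 per arm | Randomised N for 90% |
|---|---|---|---|---|---|
| 0 | 13.30 | 1.890 | – | 88.8% | 232 |
| 0.02 | 13.17 | 1.871 | 1.0% | 89.4% | 227 |
| 0.05 | 12.96 | 1.843 | 2.5% | 90.3% | 220 |
| 0.10 | 12.62 | 1.793 | 5.1% | 91.7% | 207 |
| 0.20 | 11.90 | 1.691 | 10.6% | 94.4% | 185 |

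Allowing for one O'Brien-Fleming interim at half the information lowers these slightly: 88.5% at R² = 0, then 90.1%, 91.5% and 94.3% at 5%, 10% and 20%.

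**Break-even.** AIS grade in three categories takes two parameters and linear time takes one. With 198 evaluable and about four parameters already in the model, the cost is offset when R² = 1 − (198 − 4 − 3 − 2)/(198 − 4 − 2) = 1 − 189/192 = 0.016. Below that there is no net gain.

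**Starting point.** 13.3 is the SD of change, whereas the planned model estimates a slope on baseline. Its residual SD can be no larger than that of change. As an illustration, with equal variances at both visits and an assumed baseline-to-follow-up correlation of 0.9, residual variance is (1 + 0.9)/2 = 95% of the change-score variance. That has the same effect as the 5% row, so power would be about 90.3% before either covariate is added.

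**The case against.** The strongest reply is that nothing in the plan is wrong. The model holds the baseline value of the outcome and both stratification factors. In a randomised trial, omitting further prognostic variables causes no bias and no inflation of type I error, and the confidence interval already reflects chance imbalance. All of that stands.

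Three stronger readings are tempting, and the article supports none of them.

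- A reader might take the Sample size section, which says the SD allows for excluding some complete injuries "and the delayed recruitment for up to 10 weeks after injury", as showing that completeness and delay drive variance in this trial. That text explains how an external SD was matched to the population to be enrolled. It does not say that AIS grade or days since injury predicts the 10-week score among enrolled participants once baseline motor score is known. AIS grade and motor score come from the same examination, so some of the gain may already be captured.
- A reader might see inconsistency in the AIS outcome model, which adjusts for baseline AIS grade. It does so because AIS grade is that model's outcome. This is the same rule as in the primary model.
- A reader might conclude that the trial is underpowered and that the covariates amount to free participants. The gains restate the assumed R², and the 88.8% rests on a change-score SD, so a shortfall is not shown for the planned model.

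A missing-data argument is also weak. The two covariates would make the missing-at-random assumption more plausible only if they predict both missingness and outcome, and nothing shown establishes that. Controlled imputation is already planned if more than 5% of primary outcomes are missing.

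The practical objection has force. With 128 randomised by June 2023 and an interim once 110 have completed, changing a published primary model raises timing questions. It is answerable, because the investigators and trial staff stay blinded to the interim results.

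**Conclusion.** The point holds as a low-severity efficiency improvement. The written primary model is valid and unbiased. It leaves out two pre-randomisation variables that are recorded and not stratified on, and including them follows the plan's own reason for baseline adjustment.

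The size cannot be derived from the article. For an assumed partial R² of 2% to 20%, the SE falls by 1.0% to 10.6%, and fixed-sample power rises from about 88.8% to between 89.4% and 94.4%. The true starting power may be higher. If the two variables explain less than about 1.6% beyond the planned covariates, nothing is gained, and the loss is trivial. The figures assume a two-sided test, 1:1 allocation and 198 evaluable participants.

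The missing AIS main effect in the subgroup model does not depend on any assumed R². It follows from a literal reading of the text and needs correcting in either case.

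**What to change.** In the SAP or a protocol amendment, dated before the investigators are unblinded, add to the primary model as fixed effects baseline AIS grade (A, C, D) and days from injury to randomisation (continuous). Specify the same model for any interim look not yet done. If the interim has already taken place, record which model it used. Keep the currently written model as a named sensitivity analysis.

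State that the subgroup model includes the main effect of type of SCI as well as its interaction with group. Because the secondary analyses borrow the primary model, say whether they take the two added covariates too.

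The cost is about three degrees of freedom, a few sentences of text and the administration of changing a published model in a running trial. No new data are needed.

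### The condition given for an unbiased primary analysis is broader than the model supports, and the 5% trigger for the missing-data sensitivity analysis cannot see imbalance between arms

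*Protocol article*

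**What the plan says.** Under Primary outcome measure, the protocol article sets a single time point: "The primary outcome is Total Motor Score (/100 points) 10 weeks after randomisation". Under Outcome measures it adds that "motor and sensory scores and AIS grades will not be collected at 6 months", because that visit is by telephone.

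Under Data analysis, Primary outcome, the model is specified in two sentences: "Total Motor Score at 10 weeks will be regressed on randomised group, baseline severity of injury (a stratification variable), and baseline motor score", and "Site (a second stratification variable) will be included as a random effect". On missing data it says "The primary analysis will be performed without replacing missing data", followed by the claim "It will be expected to provide unbiased estimates of the intervention effect if data are missing at random conditional on non-missing data". The fallback is conditional: "In case of non-negligible amounts of missing primary outcome data at 10 weeks (>5%), we will use controlled multiple imputations", used to find under what conditions the result would change and how plausible those conditions are. The text does not say whether the 5% is counted over the whole trial or within each arm.

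**The concern.** The word mixed refers here only to a random site effect. There is one post-baseline motor score per participant and no later one, so nothing carries information for a participant who misses the 10-week assessment. The secondary outcomes measured at both 10 weeks and 6 months differ: their models include both visits and a patient intercept, so a participant with one visit missing still contributes.

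The primary analysis is therefore a complete-case regression. It is protected when missingness depends on group, severity, baseline motor score and site. It is not protected in general when missingness depends on other recorded data that predict the outcome. The trial records several such variables: baseline AIS grade, delivered therapy time, time to discharge, and SCIM-III and WISCI-II at 10 weeks and 6 months. A participant can miss the face-to-face visit and still give 6-month function data by telephone.

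The trigger is a separate matter. Read in the natural way, as a trial-wide percentage, it ignores how losses divide between arms, and that division largely determines the bias. Only one arm receives 12 extra hours of training a week, so unequal loss is conceivable. At stake is an imbalanced loss that passes below the trigger, with the stated condition offering more reassurance than the model can give.

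**Working it through.** **Inputs from the protocol article.** Sample size: 220 participants, a 6-point difference, an SD of change of 13.3, a 10% loss allowance in both groups, alpha 0.05 and 90% power. Data analysis: the four model terms and the 5% trigger. **Assumed:** 1:1 allocation (110 per arm; the ratio is not stated), a two-sided test, and 13.3 used as the residual SD.

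**The plan's own figure.** With 99 per arm after 10% loss, two-sided power for 6 points at SD 13.3 is 88.8%, within 2 points of the stated 90%. In the other direction, 104 per arm are needed, and 208/0.9 rounds up to 232 rather than 220. Nothing below depends on that gap; 13.3 and 220 serve only as inputs.

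**Trigger arithmetic.**
- 0.05 × 220 = 11. Eleven missing is 5.0%, which is not more than 5%.
- If all 11 are in one arm: 11/110 = 10% of that arm and 0% of the other.
- A per-arm rule would respond at 6 losses in an arm: 6/110 = 5.5%.

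**Bias below the trigger.** Let f1 and f0 be the fractions missing in each arm, and d1 and d0 the departures (the mean difference between the missing and what the model predicts for them). The treatment effect is shifted by about f1·d1 − f0·d0 in absolute size. With f1 = 0.10 and f0 = 0, this is 0.10 × d1:

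| Assumed departure | Shift | Share of 6 points |
|---|---|---|
| 6 points | 0.60 | 10% |
| 6.65 points (0.5 SD) | 0.67 | 11% |
| 13.3 points (1 SD) | 1.33 | 22% |
| 26.6 points (2 SD) | 2.66 | 44% |

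**Scale against precision.** SE = 13.3 × √(1/99 + 1/110) = 1.84. The 0.5 SD case is 0.67/1.84 = 0.36 SE. The smallest significant difference is 1.96 × 1.84 = 3.61. Making an observed 6 just non-significant needs (6 − 3.61)/0.10, about 24 points of departure. Erasing it needs 6/0.10 = 60 points.

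**Simulation of the mechanism.** There were 3,000 trials per scenario, N = 220, true effect 6, residual SD 13.3, and 15 sites fitted as fixed indicators for speed. Losses were 11 in the training arm unless stated. The Monte Carlo error of each complete-case mean is 0.03 to 0.04. The last column uses single regression imputation, enough to check the point estimate.

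| Missingness depends on | Full data | Complete case | Imputed with auxiliary |
|---|---|---|---|
| Baseline score (in the model) | 6.04 | 6.04 | 6.04 |
| Auxiliary outside the model, correlation 0.5 with the residual | 5.97 | 4.97 | 5.97 |
| Same, correlation 0.8 | 6.02 | 4.41 | 6.01 |
| Same, correlation 0.8, 5% lost in each arm | 6.04 | 6.05 | 6.04 |

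The second and third rows show a bias of about 1.0 and 1.6 points (17% and 27% of 6). Divided by 0.10, these equal departures of about 10 and 16 points, so they represent strong selection. The correlations and selection strength are assumptions. The last row shows that a mechanism shared by both arms cancels; the formula shows that it would not cancel if the departures ran in opposite directions.

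**The case against.** **On the sentence.** It follows directly from the model specification and does not say all non-missing data. If it means the non-missing data that enter the model, it is correct, and the first simulation row bears this out. A reader might infer that the claim is simply false; the text does not support that. What stands is that the wording is open and, taken literally, too broad.

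**On the planning allowance.** A reader might infer that the plan's own 10% loss could bias the result unexamined. It could not: 10% exceeds 5%, so the controlled imputation would run. A simulation can give a larger bias there. For example, let 20% of participants carry an early-stop or early-discharge flag, with outcomes 0.5 SD worse in training and better in usual care, and with 40% missing if flagged and 2.5% otherwise (0.20 × 0.40 + 0.80 × 0.025 = 10%). This gives +0.9 points. But that case is above the trigger, and its opposite effects by arm are assumed. It illustrates the wording issue, not a gap in the trigger.

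**On plausibility.** Stopping training is not loss of the outcome: the Discussion accepts departures from the schedule within the intention-to-treat analysis. Eligibility requires an expected 10-week inpatient stay, the assessment has a window of two weeks either side, and nothing says that assessment ends at discharge. No figure in the document links either event to a missed score. This stands, and it makes 11 losses to 0 an edge case.

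**On scope.** Auxiliary variables and denominators are often left to the analysis plan, and the article does not forbid the analysis at 5% or below. That is fair, and their absence is not the criticism. The unbiasedness condition and the conditional trigger are both stated here, and both can be improved as stated.

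**Conclusion.** The point holds in a limited form. The primary analysis is complete-case, and its unbiasedness should be tied to group, severity, baseline motor score and site; the present wording can be read as promising more. The 5% trigger, if trial-wide, lets up to 11 one-sided losses pass without a sensitivity analysis although they are 10% of an arm.

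The consequence is modest: 0.67 points for an assumed 0.5 SD departure, and about 1.0 to 1.6 points under strong assumed selection, which is still below one standard error. A reader might infer that the primary conclusion is at risk below the trigger. The figures do not support that, since about 24 points of departure would be needed to turn an observed 6-point effect non-significant. These sizes rest on 1:1 allocation, all losses in one arm, SD 13.3, and departures that the document does not give.

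**What to change.** State the assumption as missing at random given group, severity of injury, baseline motor score and site.

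Run the controlled multiple imputation as a sensitivity analysis whatever the percentage missing. If a threshold is kept, say that it applies when either arm exceeds 5%. Running it regardless is preferable, because a count by arm still misses equal losses with opposite departures.

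Impute separately by arm, with baseline AIS grade, delivered training time, discharge date, and 10-week and 6-month SCIM-III and WISCI-II as auxiliaries. The post-randomisation variables belong in the imputation model only, not as covariates in the treatment-effect model, because the intervention may affect them. Use this imputation as the base from which the controlled departures are applied. The complete-case model stays primary.

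The cost is a wording change and modest extra analysis. All the auxiliaries are already collected, so there is no new burden on participants or sites. The change should be settled before investigators see outcomes by arm.
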